##### Revised Acquired Capability of Suicide Scale (ACSS-FAD)

The ACSS-FAD [42] instrument assesses fearlessness of death, with seven items using a 5-point rating scale (1 = “does not apply at all to me”, 5 = “applies completely to me”). It had a good internal consistency (α = .79) in a German student sample.

##### Beck Depression Inventory (BDI-II)

The BDI-II [43] is one of the most used inventories to examine the severity of depression during the 2 weeks preceding the test. There are 21 symptom groups, and participants chose one statement out of four to seven response categories (coded 0, 1, 2, and 3) per symptom. Sum scores of 29 indicate severe depression. Internal consistencies were α = .90 in a healthy sample and α = .93 in a client sample, respectively.

##### Beck Scale for Suicide Ideation (BSS)

Suicidal thinking is assessed with the BSS [44, 45], which has 21 symptom groups, each with three different response categories, representing a 3-point rating scale. The first five groups are for screening purposes and the last two groups are not included in the total BSS sum score. Higher sum scores (range 0–38) indicate a higher risk of suicide. The internal consistency in a non-clinical German sample was very good (α = .94).

#### Secondary outcomes

As secondary outcomes, prolonged grief disorder, PTSD, hopelessness, anxiety, perceived stigmatization, and perceived social support will be assessed post treatment, at 3-month follow up, and 6-month follow up. These variables will be assessed using the following instruments:

##### Short version of the Patient Health Questionnaire (PHQ-D)

The short version of the PHQ-D [46] is a 15-item screening test for depressive disorders (nine items, 4-point rating scale: 1 = “not at all”, 4 = “almost every day”), panic disorders, (i.e. panic attacks, five items, dichotomous rating scale: 1 = “no”, 2 = “yes”) and psychosocial impairment (one item, 4-point rating scale: 1 = “not at all impaired”, 4 = “very impaired”). Graefe, Zipfel, Herzog, and Loewe [47] report a satisfactory Cronbach’s alpha of α = .88 for the depression scale of the PHQ-D in a German clinical sample.

##### Screening for Complex PTSD (SkPTBS)

The SkPTBS [48] is a screening instrument for complex PTSD, with 34 items including traumatic events (self or witness) and reactions to the most distressing event, on a 7-point rating scale (1 = “not at all”, 7 = “completely”). The internal consistency was α = .91 in a German clinical sample.

##### Revised Impact of Event Scale (IES-R)

We will assess posttraumatic stress reactions within the last 7 days using the IES-R [49], which consists of the three subscales *intrusion* (seven items), *avoidance* (eight items), and *hyperarousal* (seven items) and uses a 4-point rating scale (1 = “not at all”, 4 = “often”). Internal consistency for each subscale was reported for patient groups and vary between α = .71 and α = .90.

##### Posttraumatic Cognitions Inventory (PTCI) 50]

The German version of the PTCI [50] is a 33-item questionnaire that assesses dysfunctional cognitions of traumatic events on a 7-point rating scale (1 = “totally disagree”, 7 = “totally agree”). In a clinical sample, the three subscales - negative cognitions about the self (21 items), negative cognitions about the world (seven items), and self-blame (five items) – have been shown to have satisfactory to very good internal consistency: α = .97, α = .88, and α = .86, respectively.

##### Inventory of Complicated Grief (ICG-D)

The German version [51] of the ICG [52] measures the extent of complicated grief symptoms (synonyms: prolonged grief, persistent complex bereavement disorder [53];) with 19 items on a 5-point rating-scale (1 = “never”, 5 = “always”). Cronbach’s alpha was .87 in a clinical sample.

##### Grief Experience Questionnaire (GEQ)

The GEQ [54] is a questionnaire that measures reactions to grief and symptoms that are typical in suicide bereavement. In the current study, only the stigmatization subscale is used. This scale has 10 items on a 5-point rating scale (1 = “never”, 5 = “almost always”) with a good Cronbach’s alpha value (α = .86) in a sample of bereaved students. The original items were translated into German by the last author and another research assistant using back and forth translation (see Additional file 3).

##### Stigma of Suicide and Suicide Survivor (STOSASS)

To evaluate the level of perceived stigmatization towards completed suicide, we applied the STOSASS [55], which comprises the two subscales “stigma towards the suicidal person” and “stigma towards the suicide survivor”. Participants indicate their agreement with 17 items on a 4-point rating scale (1 = “strongly disagree”, 4 = “strongly agree”). Internal consistency for the subscales in non-clinical and clinical samples was good (between .79 to .83). The original items were translated into German by the last author and another research assistant using back and forth translation (see Additional file 4).

##### H-Scales

The H-Scales [56] are a German translation of the Beck Hopelessness Scale proposed by Beck, Weissman, Lester, and Trexler [57]. The short version with 10 items to measure the participants’ negative expectations of themselves, the environment and their future life on a six-point rating scale (1 = “completely wrong”, 6 = “completely correct”) will be used. Cronbach’s alpha ranged between α = .74 and α = .92 in clinical and non-clinical samples.

##### Berlin Social Support Scales (BSSS)

The BSSS [58] assesses social support using five subscales: perceived available social support (eight items, α = .83), actually received social support (eleven items, α = .83), need for support (four items, α = .63), mobilization of social support (five items, α = .819, and protective buffering (six items, α = .82). The questionnaire was validated in a clinical sample and uses a 4-point rating scale (1 = “is not correct”, 4 = “is completely correct”). In the current study, only the subscales for perceived available social support, need for support, and mobilization of social support will be used.

##### Questionnaire on Police Delivery of Death News (QPDDN)

The QPDDN ([name] and [name]) is a newly constructed questionnaire to examine how mourners perceive the behavior of police officers who transmit the news of the death. The questionnaire consists of 34 items with items of perceived stigmatization, experienced emotional support, and perceived behavior of the police (see Additional file 5) with two items using a 6-point rating (1 = “not correct at all”, 6 = “completely correct”). Seven items assess additional information on information material received, how the message was delivered, if there was any support (e.g. doctor, pastor), which behavior they found most disturbing and what they would have wished for. Information on the validity and reliability will be provided once the data have been analyzed.

#### Process measures

In addition to the primary and secondary outcomes, we are also interested in variables that relate to the therapeutic process and the development of suicidal or depressive markers from one treatment session to another. We expect that the depressive and suicidal symptoms will reduce over the course of the intervention. After each session, depression will be assessed using the depression subscale from the PHQ-D [46]. Suicidality will be measured using the “suicide item” from the BDI-II [43].

Furthermore, the therapeutic relationships within the intervention groups are assessed using the German version of the Group Questionnaire (GQ-D) [59]. This inventory consists of subscales for positive bonding relationship (α = .92), positive working relationship (α = .89), and negative relationship (α = .79) and differentiates between group members, group leaders, and the group as a whole. Agreement with the statements is indicated on a 7-point rating scale (1 = “is not correct at all”, 7 = “is completely correct”).

### Data management and storage

#### Personal data

As part of the registration process, participants provide their name, telephone number, email address, and home address. This information is pseudonymized using encrypted codes. The pseudo-anonymization will be saved in a coding list, recorded on paper and only in one version. This list will be locked up with no third-party access. As long as the coding list exists, the study participants are able to request the deletion of all data collected from them. The coding list will be destroyed after data collection. Then all data from the study will be completely anonymous and the personal data of participants can no longer be identified.

Furthermore, we assess sociodemographic data, symptoms of general psychopathology, grief, or suicidality within the telephone interview and the online surveys. We conduct all surveys using the program Unipark®. The study-related data are stored and evaluated according to legal provisions, without the participants name or IP address. The data will be transferred to the statistical program SPSS 20. We keep the data in a place to which only employees of this study have access. We store the digital data on secured servers at the Medical School Berlin for at least 10 years. We will delete the data once the retention obligation has expired.

The audio recordings that were made in the context of the focus groups will be deleted after the transcription has been completed. The transcription has been anonymized. There will be no biological specimens collected at any time.

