### Monitoring, ethical considerations, and safety

The group leaders record each session so that the study employees can randomly examine the adherence to the intervention manual. In addition, the group leaders document each session (e.g. attendance, mood of participants, disturbances) and contact participants individually via the study online portal in the case of absence, problematic behavior, suicidality, or deterioration of symptoms. In addition, the study employees receive an automatic email when participants report increased levels of suicidality in the questionnaires after each session. If suicidality or adverse effects are suspected, the study employees will call the participants once a week to monitor and assess their mood and offer support.

The randomized controlled trial was approved by the ethics committee of Medical School Hamburg (03.03.2018). Participants are informed in writing (i.e. study information, consent form) about the procedure of the program, the aims of the study, the inclusion and exclusion criteria, risks and costs of participation, confidentiality, and data storage. They have the opportunity to drop out of the program at any time without giving reasons. They are also allowed to use other assistance (e.g. psychotherapy) in addition to study participation.

The participants are also informed about the possibility of detecting abnormalities in the clinical interview (before treatment) or during the data analysis. In that case, we contact participants for a more detailed clinical assessment. If we find clinically relevant aspects or diagnoses, the participants will be informed. However, we point out that study assessments do not substitute clinical diagnosis by a medical doctor or psychotherapist.

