During treatment, participants may experience a worsening in mood and sadness at first when they deal with the suicide of their loved ones. Such mood aggravations are normal in an intensive grief process and usually exist only for a short time. In the case of acute suicidality (i.e. corresponding hints in the suicidality item of the BDI-II), we contact the participant by telephone and offer counseling. He or she may be excluded from the program and referred to local professionals. However, the scientific evidence so far suggests that the proposed online program can reduce difficulties in coping with grief reactions and symptoms. Hence, we do not expect any unwanted side effects or lasting psychopathological worsening at the end of the program. Additionally, a supervisor will provide clinical supervision every fourth session to ensure treatment adherence and provide clinical support.

There will be no external data monitoring committee because the Sponsor and cooperation partners will function whereby procedures, results, and modifications have to be communicated on a regular basis (at least twice annually). Although the execution of the study and the data analyses are independent of these institutions, we will write several interim reports about the achievement of project aims, results, and finances and justify deviations. If adverse events arise in the suggested procedures (e.g. eligibility criteria, randomization strategy, parts of the intervention, etc.) the study coordinators will discuss the necessity and impact of possible changes to the study protocol. An audit is not scheduled in our study.

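### The only coding list is destroyed after data collection, so the promised contact over abnormalities found in the data analysis cannot be made for anything first noticed after that

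*Protocol article*

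**What the plan says.** The Personal data section of the protocol article describes pseudonymisation through a coding list kept as a single paper copy under lock. It then states "The coding list will be destroyed after data collection". After that the data are fully anonymous and "the personal data of participants can no longer be identified". The right to have data erased is tied to the same list: "As long as the coding list exists, the study participants are able to request the deletion of all data collected from them".

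The section Monitoring, ethical considerations, and safety makes a commitment that needs the list: "The participants are also informed about the possibility of detecting abnormalities in the clinical interview (before treatment) or during the data analysis". The next sentence reads "In that case, we contact participants for a more detailed clinical assessment".

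The same section also describes safeguards that work while the list exists:

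- An alert tied to sessions: "the study employees receive an automatic email when participants report increased levels of suicidality in the questionnaires after each session".
- Weekly calls, with no time limit stated: "If suicidality or adverse effects are suspected, the study employees will call the participants once a week".
- For acute suicidality signalled by the BDI-II suicidality item, in a paragraph about the treatment period: "we contact the participant by telephone and offer counseling".

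The Procedure section says there is no specific provision for care after the trial. It adds that coordinators recommend psychosocial support to participants who need it after the post-trial measurements.

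**The concern.** One section commits the team to contacting participants on the strength of what the data analysis shows. Another removes the only means of doing so at a point that can come before that analysis. Suicidality and depression at 3 and 6 months are among the primary outcomes, and the Background describes people bereaved by suicide as a high-risk group for suicide. A worrying follow-up answer is therefore the kind of finding the commitment is meant to catch. If such an answer were first seen after destruction, nobody could trace it to a person, although participants had been told that they would be contacted.

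What is at stake is participant safety and the accuracy of what participants are told. The effect estimate, the tests, the type I error rate and the power do not depend on it.

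**Working it through.** The plan gives no figure to reproduce. The check is on the order of events.

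1. **The link.** There is one coding list, on paper, in one copy (Personal data). Once it is destroyed there is no other stated route from a code to a person.
2. **Destruction.** It takes place after data collection. No date or interval is given, and no condition such as completed screening or completed analysis (Personal data).
3. **End of data collection.** Symptom assessment lists measurement points T0 to T14, with T13 at the 3-month and T14 at the 6-month follow-up. Collection therefore ends with T14 of the last groups.
4. **The analysis.** Statistical analysis covers change from baseline to post-measurement and both follow-ups. The complete analysis cannot be run before the last T14 answers are in, which is also the earliest point at which the list may be destroyed.
5. **The commitment.** Contact follows if abnormalities are detected during the data analysis (Monitoring section).

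Steps 1, 2 and 5 cannot all be honoured for a finding first made after destruction. Step 4 shows that the final analysis can fall in that period.

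Which answers could be unread by then? The stated safeguards compare as follows:

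| Safeguard | Where stated | Reaches T13 and T14? |
|---|---|---|
| Pre-treatment interview | Procedure; Monitoring | No, it precedes treatment |
| Automatic email | Monitoring | Not stated; described for questionnaires after sessions (T1 to T12) |
| Telephone contact on the BDI-II suicidality item | Monitoring | Not stated; described for the treatment period |
| Weekly calls on suspicion | Monitoring | Possible, if suspicion arises while the list exists |
| Interim analyses | Statistical analysis | Possible for earlier groups; least likely for T14 of the last groups |
| Coordinators recommend support after post-trial measurements | Procedure | Yes, but how need is recognised is not stated |

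Groups form one after another, each when 10 participants are included, with recruitment from October 2018 to about May 2020. T14 answers therefore arrive staggered, and earlier groups' answers have more time to be seen. That the exposure lies chiefly in T14 of the last groups is an inference from this timing. Unread T13 answers, or T14 answers of earlier groups, would be in the same position.

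**Size.** A group has at most 10 participants. If *k* groups had unread follow-up answers at destruction, at most 10 × *k* people would have answers that could no longer be traced, and only those with an abnormality would be missed. The documents give neither *k* nor that share. With *k* = 0, as when surveys are read on receipt, the number is 0.

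**The case against.** The strongest reply is that the wording on destruction sets an earliest point and no date. A team that reads every T14 survey and only then destroys the list complies with both sections. The analysis during which abnormalities may be found could also mean scoring surveys as they arrive, or the interim analyses, both while the list exists. The consent form is an additional file that is not shown and may limit the promise. The timing of key destruction might also be set in a fuller document.

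Much of this stands, and it rules out several stronger readings:

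- A reader might infer that the list will be destroyed before the last answers are read. The text allows this but does not say it.
- A reader might infer that follow-up is without any safety response. The weekly-call sentence has no time limit, and the Procedure section has coordinators recommending support after the post-trial measurements.
- A reader might want to put a number on the participants missed. The documents do not support one. It would need an assumed number of unread groups, and the 30% dropout in Sample size is a planning assumption, not a T14 response rate.

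The reply does not remove the conflict. Both rules are stated in the article, so this is more than missing detail. The commitment refers to the data analysis without limit, and nothing in the article makes destruction wait until the last follow-up answers have been checked.

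**Conclusion.** The point holds in a limited form and is minor. As written, the contact promised over abnormalities found in the data analysis cannot be made for anything first noticed after the coding list is destroyed. That could include follow-up answers unread by then, chiefly T14 of the last groups.

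This rests on two readings of the text: that the paper list is the only link to participants, as Personal data indicates, and that the data analysis includes the final analysis, which the wording does not exclude. The number of people affected cannot be derived and may be zero.

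**What to change.** Two clauses would settle it.

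- **Personal data:** destroy the coding list only after every T13 and T14 answer on suicidality and depression has been checked, by the same rule in both arms, and any contact that is needed has been made. Extending the existing automatic email to the follow-up surveys is one way to do this. The team can set its own trigger. No particular BDI-II cut-off is required, and the limit of > 35 in the eligibility criteria is an entry exclusion, not a definition of a follow-up abnormality.
- **Monitoring, ethical considerations, and safety:** state that contact is possible only while the coding list exists, and align the participant information if it says otherwise.

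The cost is small. The surveys are already completed online, so no new data are needed. The locked list is kept slightly longer, which calls for an ethics or data-protection notification, and staff check the follow-up answers and make a few extra calls. Because the right to request deletion lasts as long as the list, participants would keep that right for the same extra time.

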### Statistical analysis

We will use repeated measures analysis of variance (ANOVA) to analyze the changes in the primary endpoint variables (suicidality and depression) and the secondary outcomes from baseline to post-measurement and the two follow-up assessments (3 months, 6 months), where the dependent variable will be the treatment condition (treatment group vs. waitlist control group). In addition, we will control for the baseline levels of depression and suicidality using analysis of covariance (ANCOVA). The predictor analyses will be conducted using the method of multiple regression. Interim analyses will be calculated to present first results before the study is finished. To control for differences between the online groups, multilevel analyses will be conducted to allow for variation between participants and online groups at level 1. The assignment to the study group (i.e., treatment, wait list) will be on level 2. Intraclass correlation will be tested to examine potential clustering effects of the online groups.

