### Sample size

We based the power and sample size estimations in the current study on results from previous studies examining the effectiveness of online bereavement interventions [34]. Assuming a between-subject effect size of *d* = 0.80, power of 0.80, alpha of 0.05 (two-sided), and a dropout rate of 30%, the within-group sample size should be at least 52 participants. Hence, we aim to include 104 participants in total.

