### Symptom assessment

During the intervention, participants are requested to complete online surveys to assess potential changes in the therapeutic process. More precisely, there are 15 measurement points (Table 1): at the initial stage (pre-assessment (T0)), after each group session (T1–T12 including a treatment mid-point assessment after 6 weeks (T6), and a post-assessment at the end of the intervention (T12)), after 3-month follow up (T13), and finally, after 6-month follow up (T14).

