#### Primary outcomes

The primary outcomes will be the level of suicidality and depression post treatment, and at 3-month and 6-month follow up. Suicidality and depression will be assessed using the following instruments.

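### The secondary outcomes are analysed as change from baseline with only baseline depression and suicidality as named covariates; adjusting each for its own baseline score would be a free gain in precision

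*Protocol article*

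**What the plan says.** All of this stands in the protocol article.

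- Statistical analysis: repeated measures ANOVA is used "to analyze the changes in the primary endpoint variables (suicidality and depression) and the secondary outcomes from baseline to post-measurement" and the two follow-ups, "where the dependent variable will be the treatment condition".
- The next sentence adds an ANCOVA: "we will control for the baseline levels of depression and suicidality using analysis of covariance (ANCOVA"). It names no other baseline and does not say which outcomes it covers.
- The same section plans multilevel analyses to allow for differences between online groups.
- Primary outcomes: "The primary outcomes will be the level of suicidality and depression post treatment, and at 3-month and 6-month follow up". These are the same two constructs as the named covariates.
- Secondary outcomes: "prolonged grief disorder, PTSD, hopelessness, anxiety, perceived stigmatization, and perceived social support will be assessed post treatment" and at both follow-ups. The PTCI (posttraumatic cognitions) is listed among their instruments.
- Symptom assessment: the first measurement point is "at the initial stage (pre-assessment (T0"). Since the secondary outcomes are to be analysed as change from baseline, their T0 scores are part of the plan.
- Randomization: whole groups of 10 are allocated, without stratification.

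**The concern.** For most symptom scales the best single predictor of the post score is the same scale's baseline score. The plan names covariates, but for the secondary outcomes they belong to other scales. The own baseline is used only by subtraction, which fixes its coefficient at 1 instead of estimating it. With a pre-post correlation below 1, that wastes precision and over-corrects any chance difference between the arms at baseline.

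It matters more here because the units randomised are whole groups: 104 participants in groups of 10 make about 10 to 11 units, so baseline balance rests on few allocations.

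The section also swaps the roles of outcome and treatment. Read literally, the sentence describes a model that nobody would fit.

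**Working it through.** **Inputs from the protocol article.** 52 per arm, 104 in total, 30% dropout (Sample size); groups of 10 (Randomization). The sample size ("Assuming a between-subject effect size of *d* = 0.80") uses no baseline covariate, so there is no stated precision figure to reproduce. As a check on that section, its inputs give 26 per arm by t-test, and 26/0.7 = 37.1, so 38 after dropout rather than 52. That is a separate matter and does not bear on this point.

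**Assumptions (the documents give none).** r is the correlation of an outcome's baseline with its post score, 0.5 to 0.7. rho is the correlation of that baseline with baseline depression/suicidality, taken as one covariate, 0.3 to 0.7. The covariate is related to the post score only through the outcome's own baseline, so its correlation with the post score is r × rho. Pre and post variances are equal. Clustering is ignored.

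**Residual variance, relative to the unadjusted post score.**
- ANCOVA on own baseline: 1 − r²
- Change from baseline: 2(1 − r)
- Change adjusted for the stated covariate: 2(1 − r) − (r·rho − rho)²

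| r | Own-baseline ANCOVA | Change | Ratio | Change + stated covariate (rho 0.3 / 0.5 / 0.7) | Ratio |
|---|---|---|---|---|---|
| 0.5 | 0.75 | 1.00 | 1.33 | 0.978 / 0.938 / 0.878 | 1.30 / 1.25 / 1.17 |
| 0.6 | 0.64 | 0.80 | 1.25 | 0.786 / 0.760 / 0.722 | 1.23 / 1.19 / 1.13 |
| 0.7 | 0.51 | 0.60 | 1.18 | 0.592 / 0.578 / 0.556 | 1.16 / 1.13 / 1.09 |

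Worked example at r = 0.6, rho = 0.3: 0.80 − (0.18 − 0.30)² = 0.80 − 0.0144 = 0.786, and 0.786/0.64 = 1.23.

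**Power, for scale.** Completers per arm are 52 × 0.7 = 36. With an illustrative d = 0.5 and r = 0.6, own-baseline ANCOVA has power 0.74; the change analysis with the stated covariate has 0.66 to 0.69.

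**Chance imbalance.** The SD of the baseline difference between arms, in SD units, is sqrt(2/52 × (1 + 9 × ICC)).
- ICC 0: 0.196, so P(|difference| > 0.3) = 13%
- ICC 0.05: 0.236, so 20%
- ICC 0.10: 0.270, so 27%

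The ICCs are assumptions.

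Given a baseline difference D, the expected error of the treatment estimate is r·D for the unadjusted post score, (r − 1)·D for change and 0 for own-baseline ANCOVA. At r = 0.6 and D = 0.3 these are +0.18, −0.12 and 0 SD.

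**The case against.** The strongest reply is that the section is being over-read. The ANCOVA sentence repeats the two constructs just defined as primary endpoints, so its plain meaning may be ordinary own-baseline adjustment of the primary outcomes. A covariate list for secondary scales is often left to an analysis plan, and none is shown. The secondary baselines are used through the change analysis. Under randomisation, change score and ANCOVA are both unbiased, so the choice is one of efficiency.

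Much of this stands, and it limits the point. Four stronger readings are tempting, and the documents do not support them:

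- **Every outcome is adjusted for the wrong baseline.** Not so: for depression and suicidality the named covariates are their own baselines, and the fix changes nothing there.
- **Secondary post scores are adjusted only for depression and suicidality.** Under the same assumptions that would give ratios of 1.17 to 1.87. The text states no such analysis; it analyses change from baseline.
- **Calling treatment the dependent variable costs precision or balance.** It does not. The same sentence makes clear that changes in the outcomes are compared between arms.
- **Chance imbalance is likely.** 13% to 27% is possible, not likely. The upper figures need a baseline ICC of 0.05 to 0.10, and groups are formed before any session, so shared sessions cannot create clustering at T0.

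What the reply does not remove is that the article states a method and names covariates. On the stated method, no secondary outcome is adjusted for its own T0 score.

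**Conclusion.** The point holds as an available improvement for the secondary outcomes, not as a flaw in the primary analysis. Against the stated change analysis, own-baseline ANCOVA cuts residual variance by a factor of 1.25 at r = 0.6 (1.18 to 1.33 for r = 0.7 to 0.5), or about 1.09 to 1.30 once the stated covariates are added. In other words, the stated analysis needs roughly 9% to 30% more participants for the same precision. These figures rest on assumed correlations, but 2(1 − r)/(1 − r²) = 2/(1 + r) exceeds 1 for any r below 1, so the direction of the plain comparison does not depend on the value chosen.

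The better handling of chance imbalance is a second, modest benefit with about 10 to 11 randomised groups. The unstated scope of the ANCOVA and the swapped roles of outcome and treatment are wording errors to correct in the same edit.

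**What to change.** Replace the model sentences in Statistical analysis with wording to this effect: *For each primary and secondary outcome, the dependent variable is the post-baseline score. Treatment condition is the between-subject factor, the T0 score of the same scale is a covariate, and online group is a random effect in the multilevel model. The randomised comparison is at T12; the 3-month and 6-month assessments are analysed separately, as stated for each.*

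The follow-ups need their own statement and must not be dropped: they are planned outcomes, but the waitlist arm is due to receive the intervention 12 weeks after registration. Baseline BDI-II and BSS may stay as extra covariates, which keeps the adjustment the sponsor intended.

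The cost is wording only. The T0 scores are already planned, and the random effect fits the multilevel analyses already announced.
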